### Participant Timeline (18)

Participants who meet eligibility criteria after the screening survey will be invited to join the main study. After consenting to the main study, they will immediately be randomly assigned to either the training or the test group. The main study will last six weeks (more if extensions are requested), including three questionnaire batches (QB1, QB2, QB3), three task batches (TB1, TB2, TB3), and five weeks of engagement with the e-couch program (see **Figure 1** for the study design and timeline). We use the term *batch* to refer to a set of questionnaires and/or tasks administered at the same timepoint. Each batch should be completed within seven days. An additional one-week extension will be automatically allowed for the completion of each batch, and longer extensions (up to one month) may be granted upon request.

**Figure 1 f1:**
[figure not shown]
Schematic diagram of study design and participant timeline.

At baseline, participants will complete QB1 (clinical symptom measures and a matrix reasoning task; approximately 35 minutes). They will then proceed to TB1 (four behavioral tasks; approximately 65 minutes) and after one day, to TB2 (two behavioral tasks; approximately 40 minutes). After completing TB2, participants will be randomly assigned to either the BA or CR group in a 1:1 ratio and can begin their five-week engagement with the e-couch program. Each module or submodule will require approximately up to 30–60 minutes per week, and participants will be encouraged to practice skills for a full week before progressing to the next module (see Section 15a, *Intervention and Comparator* for e-couch schedule).

While working through e-couch, participants will also complete additional assessments and behavioral tasks. Before starting e-couch week 2, they will complete QB2 (clinical symptom measures; approximately 7 minutes). Before e-couch week 4, they will complete TB3 (same questionnaires as in QB2 and four behavioral tasks; approximately 70 minutes). At the end of five weeks of e-couch, participants will complete QB3 (clinical symptom measures; approximately 30 minutes) to assess post-intervention symptoms.

Follow-up of symptoms will be assessed with questionnaires at 6, 18, and 42 weeks after study completion to assess immediate, mid-term, and long-term effects of the e-couch intervention. Each questionnaire will take approximately 7 minutes. For detailed description of the questionnaires and behavioral tasks, see **Figure 2** and Section 25, *Data collection method*.

**Figure 2 f2:**
[figure not shown]
Questionnaires and tasks administered at each study phase. PHQ-9, Patient Health Questionnaire; QIDS, Quick Inventory of Depressive Symptomatology; GAD-7, Generalized Anxiety Disorder 7-item Scale; MDQ, Mood Disorder Questionnaire; PC-PTSD-5, Primary Care PTSD Screen; ASSIST-Lite, Alcohol, Smoking and Substance Involvement Screening Test; PDI, Peters Delusion Inventory; WSAS, Work and Social Adjustment Scale; WHOQOL-BREF, World Health Organization Quality of Life-BREF; WHO-5, World Health Organization-Five Wellbeing Index; AMI, Apathy-Motivation Index; PVSS, Positive Valence Systems Scale; SHAPS, Snaith-Hamilton Pleasure Scale; BADS, Behavioral Activation for Depression Scale; DAS, Dysfunctional Attitude Scale; PSWQ, Penn State Worry Questionnaire; NEO-FFI, NEO Five Factor Inventory (Neuroticism subscale); SRRS, Social Readjustment Rating Scale; MSPSS, Multidimensional Scale of Perceived Social Support; RTQ, Readiness for Therapy Questionnaire; SAI, Session Alliance Inventory; MULTI-30, Multitheoretical List of Therapeutic Interventions. References for all questionnaires and tasks are provided in section 25, *Data collection method*.

### Sample size (19)

We computed the required sample size for a multivariable prediction model with binary outcomes based on Riley et al. (39). To our knowledge, previous models are not available in the literature to anticipate Cox-Snell R2 for our study. Hence, we estimated the required Cox-Snell R2 value to be 0.05 based on pseudo-R2 values from the field of computational psychiatry, assuming small effect sizes when relating task behavior to symptom measurements (40, 41). Note, however, that this is a very conservative estimate, as we have previously found a large effect size when relating parameter estimates from the planned effort task to clinical diagnoses and a medium effect size when relating the parameters to subsequent symptom development (28). Furthermore, as we have optimized our tasks to relate to symptom changes due to therapy, we expect larger effect sizes in this study. For the sample size calculation, we also assumed a prevalence of response to iCBT of 0.5 (42), setting the shrinkage parameter to 0.9 to avoid overfitting 4–6 predictors (parameter estimates from our tasks and candidate predictors from the literature such as baseline severity (43) and gender (42)). The computed required sample size is 875 participants. We have therefore conservatively planned for a training set sample size of N = 1000. For current planning purposes, we assume that we will dedicate data from over 300 participants to the test dataset, well exceeding the recommendations for 100–200 events for validation data sets (44). Anticipating an attrition rate of approximately 20% (45, 46), we aim to recruit a total of 1,500 participants based on power analysis. We will compute the power that our test dataset provides once we have obtained results from our model development (47).

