#### Primary analyses: predicting response to CBT-based interventions

Our primary analytic goal is to predict who will benefit from CBT-based interventions and who might benefit more from BA versus CR. In line with recommendations by (84), predictors will be exclusively based on variables collected during the baseline assessment and their definition or computation will not be dependent in any way on outcome variables. Similarly, outcomes will be defined independent of any predictor variables (e.g., we will not use change scores as outcomes).

Model development will be conducted exclusively within the training data using an internal validation framework. Specifically, we will use nested, repeated 10-fold cross-validation, with the full procedure repeated 100 times to improve the stability of performance estimates. Identical cross-validation splits will be used across all candidate models to enable fair model comparisons.

To develop our models, we will first perform systematic variable selection and exploratory modeling on the training dataset using cross-validation to assess consistency and prevent overfitting. We will add to the models groups of related predictors (such as demographic variables, clinical variables, task-derived variables) that would be presumably assessed jointly in a clinical setting and subsequently use automated feature selection and regularization to determine which predictors to include in the final model. Predictor selection will be treated as part of the model development process and conducted exclusively in the training data. The finalized predictor set for each model and time point will be fixed and preregistered prior to confirmatory evaluation on the held-out test data.

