Second, we will add task-derived variables from each task separately to the baseline model to test whether these variables improve the predictive accuracy. For each set of task variables that we find to improve predictive accuracy, we will preregister the corresponding analyses for confirmation in the test dataset. We take this single-task approach as we consider each task as a separate instrument to be tested for efficacy independently, and to improve clinical feasibility (as one 15-minute task is clinically more feasible than a two-hour task battery) and interpretability (as some tasks assess correlated features, so combining them could obscure which variables drive the effects).

We will take this two-step approach both when examining how well we can predict whether an individual will respond to CBT-based interventions, and whether we can differentially predict whether they will benefit more from BA vs CR. For algorithms aiming to predict depression scores at week six after engaging with any CBT-based interventions, the final outcome will be out-of-sample predictive accuracy above chance (for the baseline model) or above the baseline model (for models including task data). For algorithms predicting differential outcome for behavioral vs. cognitive interventions, we will train algorithms for each arm separately. Following the approach of the personalized advantage index (PAI; 88, 89), we will use the model to predict for each participant the outcome for the intervention they received (using models trained on data not including this participant) and for the one they did not receive (counterfactual outcome). The final outcome will constitute whether individuals who were predicted to have received their more beneficial outcome have lower depression scores at the 6-week mark than those who the algorithm predicts would have fared better from the other intervention (and how much that difference improves by adding in task parameters).

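### The required 875 is the figure for five predictors in one pooled model: it does not cover six, and it does not apply to the BA-versus-CR models, which are trained per arm on about 380–500 people each

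*Protocol article*

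**What the plan says.** Section 19 (Sample size) sets out a single calculation: "We computed the required sample size for a multivariable prediction model with binary outcomes". Its inputs are an explained variation for which "we estimated the required Cox-Snell R2 value to be 0.05", an outcome frequency ("we also assumed a prevalence of response to iCBT of 0.5"), and a shrinkage target, "setting the shrinkage parameter to 0.9 to avoid overfitting 4–6 predictors". The result is one number: "The computed required sample size is 875 participants". The authors then "conservatively planned for a training set sample size of N = 1000". The section does not say which number of predictors produces 875, and it does not mention models fitted within an arm.

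Trial design (12) names two primary goals: predicting benefit from CBT-based interventions overall, and finding what moderates BA against CR. For the second goal, the primary analyses in section 27a state that "we will train algorithms for each arm separately" and then compare each participant's predicted outcome under the two interventions. For model building, the same section adds groups of demographic, clinical and task variables and will "subsequently use automated feature selection and regularization to determine which predictors to include in the final model".

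**The concern.** A prediction-model sample size depends directly on the number of predictor parameters, so one figure cannot serve a range of 4–6 unless it is the figure for six. It is also specific to one model. Two models, each fitted to half of the training set, each need their own calculation, and section 19 has none for the second primary goal.

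The personalised advantage index subtracts one arm's prediction from the other's, so overfitting in either model enters the predicted BA–CR difference. A reader of section 19 would reasonably think that the training set had been sized for both primary goals. The size of the gap for the arm-specific models is stated nowhere.

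**Working it through.** **Inputs.** From section 19: R2 = 0.05, prevalence 0.5, target shrinkage S = 0.9, P = 4 to 6 predictors, 1,500 recruited, about 20% attrition, planned training N = 1,000. From the Abstract: a 2:1 training-to-test split. From Trial design (12): 1:1 allocation to arms. From Eligibility criteria (14a) and section 27b: about 95% have PHQ-9 above 4 and only these enter the prediction analyses. From section 27c: outcomes are not imputed, so participants without a week-6 outcome do not contribute.

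**Reproducing 875.** The shrinkage criterion for a binary prediction model is n = P / [(S − 1) ln(1 − R2/S)]. Here ln(1 − 0.05/0.9) = −0.05716 and (0.9 − 1) × (−0.05716) = 0.005716, so each parameter needs 1/0.005716 = 174.95 participants.

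- P = 4: 699.8, so 700
- P = 5: 874.8, so 875
- P = 6: 1,049.7, so 1,050

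The two companion criteria do not bind. Limiting optimism in R2 (maximum R2 = 1 − 0.5² = 0.75) needs about 127 at P = 5. Estimating overall risk to within 0.05 needs (1.96/0.05)² × 0.25 = 384.2, so 385. The protocol's 875 is therefore the P = 5 value.

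**Training participants per arm.** 1,500 × 2/3 × 0.8 / 2 = 400, and 400 × 0.95 = 380 after the PHQ-9 restriction. The protocol does not state this figure; it assumes attrition falls evenly over the split and the arms. Taking the planned 1,000 as fully analysable gives 500. Allowing for the first 100 participants all being assigned to training (section 28) gives (100 + 1,400 × 2/3) × 0.8 / 2 = 413, which lies between the two.

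**Expected shrinkage.** Solving the same formula for S at R2 = 0.05:

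| n for the model | P = 4 | P = 5 | P = 6 | Parameters supported at S = 0.9 |
|---|---|---|---|---|
| 380 per arm | 0.830 | 0.797 | 0.766 | 2.17 |
| 400 per arm | 0.838 | 0.805 | 0.775 | 2.29 |
| 500 per arm | 0.866 | 0.838 | 0.811 | 2.86 |
| 800 pooled | 0.911 | 0.892 | 0.873 | 4.57 |
| 1,000 pooled | 0.928 | 0.911 | 0.896 | 5.72 |

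The last column is n / 174.95. The 800 is 1,500 × 2/3 × 0.8. Every per-arm entry is below 0.9, and only two parameters per arm meet the target. The pooled entries are at or close to it.

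**Sensitivity to R2.** At 400 per arm, S = 0.9 requires R2 of 0.086, 0.106 and 0.125 for P = 4, 5 and 6. At 500 per arm it requires 0.069, 0.086 and 0.102.

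**Candidates.** The documents give no count of candidate parameters per model. With 20 as an illustration, the requirement at R2 = 0.05 is 20 × 174.95, about 3,500 per model. S at 400 would be 0.51, and R2 of about 0.35 would be needed to reach 0.9.

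**The case against.** Several points on the other side are sound.

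- The figure of 875 is not confined to five predictors, since it also covers four. At the planned N = 1,000 the shortfall for six is only 0.004. For the pooled model at that size the issue is mainly one of labelling.
- Section 19 makes no explicit claim about the per-arm models. A reader might infer that the BA-versus-CR aim has no protection against overfitting, or that recommendations are bound to be too extreme. The documents do not support either. Section 27a plans lasso or elastic net, nested 10-fold cross-validation repeated 100 times, calibration on inner-loop predictions, and a preregistered pipeline tested on held-out data. The shrinkage values above do not account for these steps.
- Section 19 calls R2 = 0.05 very conservative. It was set for a binary outcome, whereas the BA-versus-CR comparison uses week-6 depression scores and baseline severity is a named predictor. The documents give no baseline-to-week-6 correlation. If it were 0.33, baseline severity alone would give R2 of about 0.33² = 0.109, enough for five prespecified predictors at 400 per arm.
- One could count every listed sociodemographic item, scale and task (about 44) and conclude that about 7,700 participants are needed. That is not a model in the plan: it treats instruments as parameters and pools all the tasks, while section 27a adds each task separately to the baseline model.

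What remains is that none of these safeguards makes 875 apply to a model fitted on half of the training set. A larger R2 rescues a small prespecified set of predictors, but not selection from a much larger pool.

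**Conclusion.** The point holds as a mismatch of scope; the arithmetic itself reproduces exactly. The figure of 875 is the requirement for five predictor parameters in one pooled model. It covers four, and it falls 175 short at six (1,050 − 875).

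For the arm-specific models, expected shrinkage for 4–6 predictors is about 0.77–0.84 at 380–400 per arm and 0.81–0.87 at 500, below the 0.9 target throughout. This rests on two assumptions that the protocol does not state: that R2 = 0.05 also holds within each arm, and that arm models have 4–6 predictors. Within-arm R2 of about 0.09–0.13 would meet the target at 400 per arm for prespecified predictors.

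What is missing for the BA-versus-CR goal is the sample-size guarantee of S = 0.9, not every control on overfitting. It should be fixed, but it does not undermine the conduct of the trial.

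**What to change.** In section 19:

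1. State that 875 is for five predictor parameters in one pooled model, and that six needs 1,050.
2. Add the training number expected per arm (about 380–400, or 500 if all 1,000 are analysable) and the expected shrinkage, over a range of R2 that includes 0.05 and values around 0.09–0.13.
3. Limit the S = 0.9 statement to the pooled model.
4. Count candidate rather than retained parameters when the per-arm candidate set is fixed, before preregistration.

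The choice between per-arm and pooled modelling can stay with the training-set work. A pooled model with interactions is not an automatic cure. Five shared terms, arm and two interactions make 8 parameters, which need 1,400 and give S of about 0.84 at 800. With all five interactions there are 11 parameters, which need 1,925 and give about 0.79.

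The cost is a rewritten paragraph and a less favourable stated figure. No recruitment or data collection changes, and the work can be done before the test set is opened.

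### At the plan's own 50% response rate, a test set of 300 participants is about 150 events: inside the cited 100–200 events, not well above it

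*Protocol article*

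**What the plan says.** All the key statements are in Sample size (19) of the protocol article. The outcome type is fixed first: "We computed the required sample size for a multivariable prediction model with binary outcomes". The inputs are a Cox-Snell R² of 0.05, a response rate ("we also assumed a prevalence of response to iCBT of 0.5"), and a shrinkage target ("setting the shrinkage parameter to 0.9 to avoid overfitting 4–6 predictors"). The result is that "The computed required sample size is 875 participants", rounded up to a training set of 1,000.

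For the test set there is no calculation. The plan states that "we assume that we will dedicate data from over 300 participants to the test dataset", and judges this number as "well exceeding the recommendations for 100–200 events for validation data sets". The section then allows for about 20% attrition, sets recruitment at 1,500, and defers test-set power until the models have been developed.

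Other sections bear on how many test participants will be analysed:
- Statistical methods (27): assignment to training or test is 2:1 and takes place at consent.
- Who will be included in the analyses (27b): the predictive analyses are limited to randomised participants with baseline PHQ-9 above 4. Eligibility criteria (14a) expects these to be about 95% of the sample.
- How missing data will be handled (27c): outcomes are not planned to be imputed.
- Data monitoring committee (28): the first 100 participants all went into the training set.

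**The concern.** The two sides of the comparison are in different units. The number 300 exceeds 200 only if every participant is counted as an event. With half of participants expected to respond, the like-for-like figure is half as large.

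This matters because the held-out test set is where the preregistered models are to be confirmed, and this sentence is the only numerical support the article gives for its size. A reader would conclude that the test set has comfortable headroom above the recommended range. On the plan's own inputs that headroom is not there.

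**Working it through.** **1. The section's own figure.** The development sample size reproduces with the shrinkage criterion n = p / [(S − 1) · ln(1 − R²/S)], with S = 0.9 and R² = 0.05:
- p = 4: 699.8, rounded up to 700
- p = 5: 874.8, rounded up to 875, which matches the stated figure
- p = 6: 1,049.7, rounded up to 1,050

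The 875 therefore corresponds to 5 predictors. The unit problem does not touch this calculation.

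**2. The test set in events.** Expected events = test participants × response rate.
- 300 × 0.5 = 150 events, and 150 non-events.
- For 300 participants to give more than 200 events, the response rate would have to exceed 200/300 = 0.667, against the assumed 0.5.
- At 0.5, more than 200/0.5 = 400 analysed test participants are needed before the expected count passes 200.

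**3. How large the test set could be on the plan's recruitment figures.** I assume that the 20% attrition falls equally on training and test, and that those lost provide no outcome.

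| Reading | Test participants | Expected events at 0.5 |
|---|---|---|
| Stated minimum | 300 | 150 |
| 1,500 / 3 × 0.8 | 400 | 200 |
| As above × 0.95 (PHQ-9 above 4) | 380 | 190 |
| First 100 all in training, 2:1 on the rest: 1,400 / 3 × 0.8 | 373 | 187 |
| As above × 0.95 | 355 | 177 |
| Before attrition: 1,500 / 3 | 500 | 250 |

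The two rows with 1,400 rest on an assumption that the article does not confirm: that the first 100 count toward the 1,500 and that 2:1 applies to everyone after them.

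Only the last row passes 200, and it ignores the plan's own attrition. With 400 analysed participants, the binomial probability of observing more than 200 events is 0.48. With 380 it is 0.14.

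**4. Whether the section's sizes fit together.** Participants remaining after attrition: 1,500 × 0.8 = 1,200. Training plus test as stated: 1,000 + 300 = 1,300, which would need 1,300 / 0.8 = 1,625 recruits. A 2:1 split of 1,200 is 800 and 400, not 1,000 and 300. If 1,000 of the 1,200 were in training, 200 would be left for the test set, or 100 events. If the 1,000 is instead a count before attrition (1,500 × 2/3), then 1,000 × 0.8 = 800 remain in training, below the 875 computed. The test-set size therefore cannot be settled from the section as it stands.

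**The case against.** The strongest defence is that nothing essential fails. 150 events is half as many again as the lower bound of 100, and 177–200 lies in the upper part of the range. The test-set figure is given as a minimum, and the Abstract speaks of recruiting at least 1,500. All of this stands: the pooled test set meets the cited recommendation. It does not save the claim of a clear excess, because even 400 analysed participants give only 200 expected events.

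A reader might go further and infer that the test set is inadequate for the BA-versus-CR question, since models are trained by arm and 300 participants give only about 75 events per arm (300 × 0.5 / 2, assuming 50% response in each arm). The article does not support that inference. It never applies the 100–200 benchmark to single arms. Its stated differential outcome, in the primary analyses of section 27a, compares week-6 depression scores across the whole test set, between people predicted to have received their better intervention and people predicted to have fared better with the other. The arm-level count is context only.

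A reader might also want a detectable difference stated now. That is a preference. Sections 19 and 27 openly defer test-set power and effect size until after model development and to the preregistration, and that deferral is separate from the unit error.

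**Conclusion.** The point holds as a misstatement in section 19. A participant count is set against an events benchmark, and the claimed excess disappears once the plan's own prevalence is applied. The expected count is about 150 events at the stated minimum, and roughly 177–200 under 1,500 recruits, 2:1 assignment and 20% attrition. These figures lie within 100–200, with 200 as the ceiling. No other section corrects the statement.

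The result rests on the 0.5 response rate and the binary outcome that section 19 itself adopts. The 177–187 figures also rest on the assumption about the first 100 participants. It does not follow that the test set falls short of the recommendation or that a design feature must change. The correction is to the stated figure and to the consistency of the sizes around it.

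**What to change.** In section 19:
- Remove the claim of exceeding the recommendation, and give the expected number of test-set events: about 150 at 300 participants, or roughly 177–200 under 1,500 recruits, 2:1 assignment and 20% attrition. Describe this as within the recommended 100–200.
- Reconcile the test-set size with the training set of 1,000 and the 1,200 participants expected to remain. State whether each figure is before or after attrition, whether it counts only participants with PHQ-9 above 4, and whether the first 100 participants are part of the 1,500.
- If arm-level counts are mentioned, label them as context and state the assumption of 50% response in each arm.

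The cost is a revision of section 19 and a less favourable stated figure. Restating the figure in events requires no change to the analyses. What the reconciliation implies for recruitment or the split is for the sponsor to settle once the figures are put on the same basis.

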**Methods and analysis:**

We plan to recruit at least 1,500 adult participants who report having symptoms of depression and reside in U.S. After completing a series of questionnaires and behavioral tasks to assess their learning propensities, participants will be randomly assigned to a BA or a CR group. Using an online self-help tool, participants will then engage with designated modules according to their assigned group for five weeks. We will assess symptoms 1 week post-intervention (main end point of study) and follow up at 6, 18, and 42 weeks post-intervention. Upon enrolling and consenting into the main study, participants will be randomly assigned to either the training dataset or the held-out test dataset at a ratio of 2:1. This enables a clean separation of training and test datasets and prevent data leakage. We plan to build cross-validated predictive algorithms on the training dataset, and preregister our analysis plan before we validate our models and hypotheses in the held-out, unseen, test dataset. Enrollment of the study started 23rd January, 2024.

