### Eligibility criteria (14a)

Participants are eligible to participate only if they meet all the following criteria assessed by a screening survey at the beginning the study (see **Supplement *Study-specific measures***):

at least 18 years old,physically located in the US,fluent in English,no hearing problems,have access to headphones,have not previously participated in studies from our lab,no one from the same household has enrolled in this current study,are not currently receiving psychotherapy or have plans to begin within the next eight weeks,have not changed the dosage or type of antidepressants (if they are on any) in the last four weeks, or plan to make any such changes during the next eight weeks, andtheir primary mental health concern is to improve their mood, reduce negative thoughts, enjoy more activities again, or reduce symptoms of depression.

The above list has been updated from protocol version 1.0 after we examined the data quality from the first 100 participants (See **Supplement *Protocol changes*** for details). Our primary target population will consist of participants who self-report depressive symptoms, defined as a score greater than 4 on the Patient Health Questionnaire (PHQ-9; 35). We will oversample participants meeting this criterion, such that approximately 95% of the sample will fall within this range. Participants with a lower PHQ-9 score will be recruited for practical reasons (namely: as we do not want to encourage over-reporting of symptoms, we explicitly instruct participants that symptoms are not a prerequisite for the study; as such, we must admit to the study some participants without symptoms of depression). However, participants with a PHQ-9 score below 5 are not part of the intention-to-treat sample and will not be analyzed in primary prediction analyses (see section 27b, *Who will be included in the analyses*). To further ensure data quality, we include an attention-check question embedded within the PHQ-9 (see Section 25 *Data collection method*, for an example) and will not include participants who fail the attention check.

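### Recruiting 1,500 with a 2:1 split and 20% attrition leaves about 800 analysable training participants, below both the planned 1000 and the computed minimum of 875

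*Protocol article*

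**What the plan says.** Sample size (19) sizes a multivariable prediction model with a binary outcome. For the inputs it says "we estimated the required Cox-Snell R2 value to be 0.05", takes a response prevalence of 0.5, and describes "setting the shrinkage parameter to 0.9 to avoid overfitting 4–6 predictors". The result is given as "The computed required sample size is 875 participants". It goes on: "We have therefore conservatively planned for a training set sample size of N = 1000". It assumes over 300 participants for the test set and closes with "Anticipating an attrition rate of approximately 20% (45, 46), we aim to recruit a total of 1,500 participants based on power analysis".

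Other sections bear on the number that will be analysed:

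- The Abstract (Methods and analysis) says that "participants will be randomly assigned to either the training dataset or the held-out test dataset at a ratio of 2:1" on consenting to the main study. Objectives (10), Participant Timeline (18) and Statistical methods (27) agree on the ratio, the timing or both.
- Section 27c does not impute missing outcomes.
- Sections 14a and 27b keep participants with PHQ-9 below 5 out of the primary prediction analyses. On those above that threshold, 14a says "approximately 95% of the sample will fall within this range".
- Section 28 records that the first 100 participants all went to training.

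**The concern.** Section 19 moves from 875 required, to 1000 planned for training, to over 300 for test, to 20% attrition, to 1,500 recruited. Read in that order, 1000 and 300 are the numbers wanted after losses, and 1,500 is the recruitment that supplies them. But 1000 + 300 = 1,300, whereas 1,500 less 20% is 1,200. The 2:1 split makes the training side worse, because it sends a third of the retained participants to the test set.

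Out-of-sample predictive accuracy is the trial's primary outcome, and this is the only sample-size justification given for the models. A reader would credit the plan with a margin of 14% over its overfitting requirement (1000 against 875). If the plan's own attrition and split produce a deficit instead, the claim of adequacy is reversed. An analysis plan preregistered after data collection cannot change the number recruited.

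**Working it through.** **Inputs.** From section 19: Cox-Snell R² = 0.05, shrinkage S = 0.9, 4 to 6 predictors, attrition 20%, total 1,500. From the Abstract and sections 10, 18 and 27: a 2:1 split at consent. From section 14a: 95% with PHQ-9 above 4. From section 28: the first 100 in training.

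**Reproducing 875.** The shrinkage criterion is n = p / [(S − 1) × ln(1 − R²/S)].

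| Parameters p | Required n |
|---|---|
| 4 | 699.8, so 700 |
| 5 | 874.8, so 875 |
| 6 | 1,049.7, so 1,050 |

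The stated 875 is the five-parameter result. The method's other criteria need fewer at prevalence 0.5: 385 for estimating the overall risk to within 0.05, and 102 to 153 for an optimism of 0.05 in Nagelkerke R². Shrinkage is therefore the binding criterion.

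**Testing 1,500 as a total.** 1,300 / 0.8 = 1,625, and the cruder 1,300 × 1.2 = 1,560. Neither gives 1,500. To keep 1,300 of 1,500, attrition could be at most 1 − 1,300/1,500 = 13.3%.

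**Analysable sets under the stated plan.**

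| Assumption | Training | Test |
|---|---|---|
| 2:1 split, 20% attrition | 1,500 × 2/3 × 0.8 = 800 | 1,500 × 1/3 × 0.8 = 400 |
| Same, PHQ-9 below 5 removed (× 0.95) | 760 | 380 |
| First 100 in training, other 1,400 split 2:1 | (100 + 933.3) × 0.8 = 827 | 466.7 × 0.8 = 373 |
| Same, PHQ-9 below 5 removed | 785 | 355 |

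Against 1000, the training shortfall runs from 17% (827) to 24% (760). Against 875 it runs from 5.5% to 13%. Training reaches 875 only if attrition is at most 1 − 875/1,000 = 12.5%, or 15.3% with the first-100 credit, before any PHQ-9 deduction.

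**What these sets support.** At R² = 0.05 and S = 0.9 each parameter costs 874.8 / 5 = 175 participants. So 760 supports 4.3 parameters, 800 supports 4.6 and 827 supports 4.7: four whole parameters in each case. Solving the same formula for S gives the expected shrinkage:

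| Training n | p = 4 | p = 5 | p = 6 |
|---|---|---|---|
| 760 | 0.907 | 0.887 | 0.867 |
| 800 | 0.911 | 0.892 | 0.873 |
| 827 | 0.914 | 0.895 | 0.877 |

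**Recruitment needed at 2:1 and 20% attrition.**

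| Training target | Basic | With first-100 credit | With 95% PHQ-9 filter, no credit |
|---|---|---|---|
| 875 | 875 × 1.5 / 0.8 = 1,641 | 1,591 | 1,727 |
| 1000 | 1000 × 1.5 / 0.8 = 1,875 | 1,825 | 1,974 |

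**The case against.** Several points can be made for the plan.

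- **The 1000 may mean participants allocated.** Since 1,500 × 2/3 is exactly 1,000, this reading is possible, and it would also satisfy the test figure. It does not help with 875, which is the number needed to fit the model. With outcomes not imputed, 800 remain. On this reading the 1000 carries no allowance for the attrition stated in the same section.
- **A different split clears 875.** Taking 300 for test from 1,200 leaves 900 for training. That abandons the 2:1 ratio stated in several places and still misses 1000. The shortfall claim is therefore confined to readings that keep 2:1.
- **1,500 is worded as a minimum in the Abstract.** Over-recruitment could close the gap, but no larger target appears anywhere.
- **The PHQ-9 deduction may double-count.** The Abstract describes the 1,500 as people reporting depressive symptoms. If that means PHQ-9 above 4, no further 5% is lost. Section 14a applies its 95% to the whole sample, which favours the deduction, but the text does not settle it. The 800/400 result does not depend on it.
- **The harm is small.** This largely stands. For five predictors the target is missed by about 0.01. Four predictors, within the stated range, are adequately covered. An R² of 0.0545 in place of 0.05 would meet S = 0.9 at 800, and section 19 regards 0.05 as cautious. Development uses nested cross-validation and includes penalised models, and the test set of 355 to 400 exceeds its own plan.

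Against that last point, six predictors, the top of the stated range, would need 1,050, more than even the planned 1000. The separate BA and CR models in section 27a would each be trained on about half of 800. At roughly 400 per arm and the same inputs (an assumption), 400 / 175 = 2.3, so two parameters meet the target.

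**Conclusion.** The concern holds. On the protocol's own attrition and split, the expected analysable training set is about 800, or 827 with the first-100 credit. It falls to 760 to 785 if the PHQ-9 filter applies to the 1,500. Every version that keeps the 2:1 split is below both 1000 and 875, so section 19's description of its training set as conservative is wrong as written.

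The result rests on attrition being equal in the two sets, on 1,500 being the number consented and split, and on 875 belonging to a five-parameter model. That last point is inferred from the formula, since the text gives only a range of 4 to 6. The effect on a pooled five-predictor model is modest. The error is in the stated justification more than in the viability of the trial, and it weighs more heavily on the arm-specific models.

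**What to change.** Revise section 19 in one of two ways.

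1. **Keep 1,500 and restate what it delivers.** Give the expected analysable sets as about 800 training and 400 test (827 and 373 if the first 100 are credited to training). State whether the 1,500 includes participants with PHQ-9 below 5; if so, the figures are about 760 and 380, or 785 and 355 with the credit. Say that at R² = 0.05 this supports four predictor parameters at shrinkage 0.9, or five at about 0.89. Remove the statement that a training set of 1000 has been conservatively planned.
2. **Keep 1000 and state the recruitment it needs.** At 2:1 and 20% attrition this is 1,875, or 1,825 with the first-100 credit. With the 95% PHQ-9 filter and no credit it is 1,974.

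In either case, state that 875 corresponds to five parameters and say whether the sample-size figures count participants allocated or participants analysed.

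The first option costs wording and one recalculation, makes the stated figures less favourable, and needs no extra participants. The second needs about 325 to 474 more recruits than 1,500.
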